## Abstract

**Introduction::**

Psoriasis is a common chronic relapsing inflammatory skin disease, which may have considerable detrimental effects on the quality of life. Considering high costs and side effects associated with the use of conventional medications, acupuncture, as one of complementary and alternative nonpharmacological therapies, is commonly used in the management of psoriasis for reducing itching, repairing the skin lesions, etc. However, the effects of acupuncture in the management of psoriasis are still inconsistent, especially in psychosocial abnormality due to psoriasis. Therefore, we designed a randomized controlled trials (RCT) involving a placebo control to ensure participants’ blinding to investigate the effects of acupuncture for psoriasis in improving typical clinical symptoms and psychosocial abnormality.

**Methods::**

A singlecenter RCT was designed. 220 participants who meet the eligibility criteria will be randomly allocated into manual acupuncture group or sham acupuncture group in a 1:1 ratio. Participants will respectively receive 15 minutes manual acupuncture or sham acupuncture per session, 3 sessions per week, totally 12 weeks. Psoriasis Area and Severity Index scores, body surface area (BSA), Medical Outcomes Study 36-Item Short-Form Health Survey, Montgomery-Asberg Depression Rating Scale, and Depression, Anxiety, and Stress Scale-21 will be evaluated by blinded operators at baseline and 12 weeks. All analyses will be based on an intention-to-treat principle. The results will be published in an international peer-reviewed journal.

**Discussion::**

The results of this study are expected to clarify the effects of acupuncture on improving typical clinical symptoms and psychosocial abnormality of patients with psoriasis. It will contribute to clinical practice of acupuncture in the management of psoriasis.

**Trial registration::**

Chinese Clinical Trail Registry: ChiCTR2100045481. Registration date: April 17, 2021.

## Introduction

1

Psoriasis is a common chronic relapsing inflammatory skin disease characterized by well-delineated red and scaly plaques, which is generally associated with genetic, immunological, metabolic, and endocrinal etiologies.^[1,2]^ With a prevalence rate of 2% to 4%, psoriasis, especially for plaque psoriasis, may have considerable detrimental effects on the quality of life.^[3]^ Patients with psoriasis also usually suffer from anxiety and depression due to pruritus symptoms, sleep disturbance, etc.^[4]^ Furthermore, patients with psoriasis may have a significantly increased risk of myocardial infarction and peripheral vascular disease because of accelerated atherosclerosis in an inflammatory state.^[5]^

Management of psoriasis still faces severe challenges. Several topical treatments, including topical corticosteroids, calcineurin inhibitors, immunosuppressants, biological agents, etc, are recommended to alleviate the clinical symptom to varying degrees.^[6]^ However, high costs and obvious side effects associated with the use of these medications limit their clinical application. They are not effective for anxiety, depression, and sleep disturbance of patients with psoriasis. Therefore, more and more patients with psoriasis are seeking therapeutic benefits of complementary and alternative therapies including traditional Chinese medicine, homeopathy, cognitive hypnotherapy, etc. especially on psychosocial abnormality.^[7]^

Acupuncture, as one of complementary and alternative nonpharmacological therapies, has been commonly used in the management of psoriasis, pruritus, and dermatitis in China.^[8]^ It is associated with a low risk of side effects and adverse reaction. The review reported that acupuncture may reduce itching by accelerating the microcirculation of the local lesion area, which is conducive to the extinction of inflammation and the absorption of metabolites.^[9]^ The study also reported acupuncture may improve the immune function of the body, stimulate the function of the meridian and repair the skin lesions, then prevent the progression to chronic recurrent seizures.^[10]^ Compared with conventional medications, the meta-analysis reported that acupuncture may show a potential advantage in the management of psychosocial abnormality including anxiety, depression, and so on.^[11,12]^ It also is associated with lower recurrence rate of psoriasis.^[13]^ However, the effects of acupuncture in the management of psoriasis are still inconsistent, especially in psychosocial abnormality due to psoriasis. Most of the results come from observational studies or case reports. There is poor methodological quality in published randomized controlled trials (RCT), especially in blinding. Therefore, we designed a RCT involving a placebo control to ensure participants’ blinding to investigate the effects of acupuncture for psoriasis in improving typical clinical symptoms and psychosocial abnormality.

## Materials and methods

2

### Trial design and ethics

2.1

A singlecenter RCT was designed to compare the effects of manual acupuncture and sham acupuncture in the management of psoriasis. The study has been approved by the ethics committee of the conducted hospital (No. KY2019–541). The study protocol follows the Standard Protocol Item Recommendations for Interventional Trails guidelines. This study protocol has been funded through the Chinese Clinical Trials Register. The registry number is ChiCTR2100045481, registration date: April 17, 2021.

In the study, 220 outpatients with psoriasis will be enrolled and be randomly allocated to manual acupuncture group (n = 110, expected) or sham acupuncture group (n = 110, expected). All participants will receive 36 sessions of treatments over 12 weeks. This study will be conducted in Huashan Hospital of Fudan University from October 2021 to December 2022. The study procedure is showed in Figure 1. The trial schedule is showed in Table 1.

**Figure 1 F1:**
[figure not shown]
Flow diagram of participants.

**Table 1 T1:** Trial processes chart.

Items	Before enrollment (week -1)	Intervention period (weeks 1–12)	End of intervention (week 13)
Inclusion criteria	√		
Exclusion criteria	√		
Informed consent	√		
Baseline measurement	√		
Randomization and allocation	√		
PASI	√		√
BSA	√		√
Quality of life	√		√
Depression	√		√
Anxiety	√		√
Adverse events			√

### Patients

2.2

#### Diagnostic criteria

2.2.1

The patients with psoriasis will be diagnosed according to the 2018 China College of Dermatology diagnostic criteria: skin lesions involve ≤15% body surface area (BSA). It should be mainly located on the torso/limbs, palm/soles, and face/scalp, the vulva area should not be unaffected.

#### Inclusion criteria

2.2.2

The inclusion criteria for the study are as follows:

1.meeting the above diagnostic criteria for psoriasis;2.aged between 18 and 65 years (either sex);3.do not have history suggestive of contact allergy;4.no acupuncture within 3 weeks prior to the recruitment;5.refrained from using any other treatments from 3 weeks before acupuncture, without moisturizers;6.agreeing to participate in the trial and be randomly allocated into any study groups.

#### Exclusion criteria

2.2.3

Participants will be excluded who meet any following conditions:

1.other active skin diseases that may affect condition assessment;2.severe psychological disorders;3.pregnant or lactating women;4.serious organic disease, systemic diseases, or other chronic diseases including cardiac disease, liver, or kidney disease, thrombocytopenia with bleeding tendency;5.severe episodes of fainting during acupuncture or afraid of blood;6.experiencing other active interventions that may affect the outcome of this study during the treatment;7.any other condition that the investigators judge as likely to make the patient incapable to complete, comply, or unsuitable for the clinical trial.

#### Recruitment

2.2.4

We intend to promote the recruitment plan through multimodal strategies, including advertisements on community bulletin boards, community broadcasts, social media (WeChat), and a clinical patient database. Researchers will register the interested participants and conduct a corresponding screening assessment. Informed consent will be obtained before randomization.

#### Randomization and allocation

2.2.5

The participants will be randomly assigned to manual acupuncture group or sham acupuncture group at a 1:1 ratio after the baseline assessment. The randomization list will be generated using the Statistical Analysis Software (9.1) by a research assistant who is not involved in the recruitment of participants. The sealing and opaque envelopes will be used to achieve the allocation concealment.

#### Blinding

2.2.6

The participants, statistical analysts and assessors will be blinded to treatment allocation. In order to blind the participants, the acupoints and manipulation of needles are similar in both groups. All participants will be asked whether they have experienced manual acupuncture or sham acupuncture after the treatments to assess the blinding. It will be impossible to blind the therapists due to the characteristics of acupuncture interventions.

### Interventions

2.3

All participants will receive 36 sessions of 15-minutes duration over 12 weeks (3 sessions per week). Only trained acupuncturists will perform the acupuncture treatment, who must be instructed in standardized operating procedures including the locations of acupoints and the manipulation of needles,

#### Manual acupuncture group

2.3.1

In the study, the acupuncture needles of 0.30 mm in diameter and 40 mm in length (Suzhou Hwato Medical Instruments Co. Ltd, China) will be used. All acupoints are identified based on the point location issued by the World Health Organization. The used acupoints include SP10 (Xuehai), LI11 (Quchi), ST36 (Zusanli), SP6 (Sanyinjiao), BL13 (Feishu), BL17 (Geshu), BL18 (Ganshu), BL20 (Pishu), and LR3 (Taichong). The insertion depth of SP10, LI11, ST36, and SP6 will be 1 cun. BL13, BL17, BL18, and BL20 will be punctured 1–15 cun into the skin, and LR3 will be punctured only 0.5 cun. The procedures for acupuncture are as follows:

1.skin disinfection;2.the sterile adhesive pads will be placed on acupoints;3.acupuncture manipulation is applied to inserted through the pads for Deqi sensation including soreness, numbness, distension, pain, and heaviness sensation;4.the needles are maintained for 15 minutes for each session;5.manual stimulation is conducted 3 times every 5 minutes during each session;6.at end of each session, the needles are removed, and then clean cotton balls are pressed to avoid bleeding.

#### Sham acupuncture group

2.3.2

Blunt-tipped placebo needles (0.30 mm in diameter and 40 mm in length, produced by Suzhou Hwato Medical Instruments Co. Ltd, China) will be used in the sham acupuncture group. The schedule, locations of acupoints, and other treatment settings are the same with manual acupuncture group but with superficial skin penetration and no needle manipulation for Deqi sensation. The needles will also be maintained for 15 minutes, and sham manual stimulation will be conducted each 5 minutes during each session.

### Outcomes

2.4

#### Primary outcomes

2.4.1

The primary outcome of the current study is the proportion of patients with a reduction in the Psoriasis Area and Severity Index (PASI) scores ≥50% compared with baseline. PASI score will be evaluated at the same or closet day. Target lesions will be recorded as digital photographs by single-lens reflex cameras during each session.

#### Secondary outcomes

2.4.2

***BSA*** will be assessed by fingerprinting. The entire palm of the patient represents approximately 1% of the total BSA. The number of handprints on the psoriatic skin of the body part is used to determine the extent to which the body part is affected by psoriasis (%).^[14]^

***Quality of life*** will be assessed using the Medical Outcomes Study 36-Item Short-Form Health Survey, which consists of 36 items comprising 8 categories: functional capacity (10 items), physical aspects (4 items), pain (2 items), general health status (5 items), vitality (4 items), social aspects (2 items), mental health (5 items), and a question comparing current health conditions with those from a year ago. The total scores range from 0 to 100. High scores indicate more health status.^[15]^

***Psychosocial abnormality**depression*** will be assessed by Montgomery-Asberg Depression Rating Scale, which consists of 9 items, each rated on a 7-step Likert scale from 0 to 6.^[16]^ Higher scores indicate greater severity. It is a useful measurement for depression in clinical practice, and has good internal consistency.^[17,18]^

Anxiety will be assessed using the Depression, Anxiety, and Stress Scale-21, which is recorded on a Likert-type scale ranging from 0 (not applicable at all) to 3 (applicable very much of the time). The severity of anxiety is graded into normal, mild, moderate, severe, or extremely severe based on the scores of each domain. The Depression, Anxiety, and Stress Scale-21 showed good validity and reliability.^[19]^

#### Data collection and management

2.4.3

For the participants meeting the inclusion criteria, the research screeners will collect their baseline data at the appropriate time. The primary and secondary outcomes will be assessed by the blinding assessors at baseline and 13 weeks (within 1 week after the intervention). The research assistant, who is blind to the allocation, will complete the quality control of data collection and data entry. The research manager will complete the collection, classification, identification, and analysis of raw data.

### Statistical analysis

2.5

#### Clinical data analysis

2.5.1

In this study, clinical data will be analyzed using SPSS 19.0 statistical software by a blinded statistician. Data analysis will also be based on the intention-to-treat. Continuous variables will be showed using the mean and standard deviation, or the median and interquartile range. Categorical variables will be presented with percentages (%). A two-sample *t* test will be used in comparing clinical data between manual acupuncture group and sham acupuncture group. A paired sample *t* test will be used for comparisons between baseline and the end of treatment in each group. Clinical data on the skewed distribution will be compared using a nonparametric test. Chi-Squared test or Fisher exact test will be used for comparing categorical variables. The significance level of the test is targeted at 0.05.

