#### Sample size

2.5.2

Based on the PASI scores, the published study reported that the total curative rate in the acupuncture group was 97.5%, and 87% in the control group.^[20]^ In the current study, we assumed that a significance level α was 0.05 and a power (1-β) = 0.80, and calculated the sample size: 88 participants with psoriasis would be required in each group for 80% power to detect a difference between manual acupuncture group and sham acupuncture group using the two-sided Z test with pooled variance. The significance level of the test is 0.05. Given a 20% loss to follow-up, therefore this study will require at least 220 participants.

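### Continuous secondary outcomes: the stated between-arm test ignores the baseline values that are collected, and within-arm paired tests are added that do not compare treatments

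*Protocol article*

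**What the plan says.** Section 2.5.1 (Clinical data analysis) of the protocol article names the tests. Between arms, a two-sample t "test will be used in comparing clinical data between manual acupuncture group and sham acupuncture group". Within arms, a paired t "test will be used for comparisons between baseline and the end of treatment in each group". For data that are not normal, "Clinical data on the skewed distribution will be compared using a nonparametric test", without naming that test. For categorical data, "Chi-Squared test or Fisher exact test will be used for comparing categorical variables". No covariate appears anywhere in the section, and it does not say whether the two-sample t test is applied to week-13 values or to change from baseline.

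Section 2.4.3 (Data collection and management) says: "The primary and secondary outcomes will be assessed by the blinding assessors at baseline and 13 weeks". Table 1 agrees, with PASI, BSA, quality of life, depression and anxiety each marked before enrolment and at week 13.

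The primary outcome in section 2.4.1 is "the proportion of patients with a reduction in the Psoriasis Area and Severity Index (PASI) scores ≥50% compared with baseline". It is binary and so falls under the categorical tests.

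**The concern.** The plan collects a baseline value for each continuous secondary outcome but names no between-arm analysis that adjusts for it. Baseline usually predicts follow-up on such scales. Leaving it out makes the standard error of the treatment difference larger than the data require.

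The paired tests raise a different problem. Change within an arm combines the natural course of a relapsing disease, expectation, and any effect of needling. A significant change under manual acupuncture therefore says nothing about manual versus sham, and neither does a significant change in one arm beside a non-significant change in the other. This matters most for depression and anxiety, because psychosocial benefit is one of the trial's two declared aims and those outcomes rest entirely on the secondary analyses.

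**Working it through.** **Inputs from the article.** Two-sided alpha is 0.05 (sections 2.5.1 and 2.5.2). Evaluable patients per arm are 88 (section 2.5.2), which agrees with 110 randomised per arm and 20% loss: 110 × 0.80 = 88. That number was set for two proportions. The article states no sample size, SD or power for any continuous outcome, so there is no planned figure to reproduce here.

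**Assumed inputs.** The correlation r between baseline and week 13 is taken as 0.3, 0.5 and 0.7. The SD is taken as equal at both times, and r as the same in both arms. The degree of freedom spent on the covariate is ignored.

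**Precision.** With SD σ and n per arm, the variance of the estimated treatment difference is:

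- t test on final values: 2σ²/n
- t test on change: 2(1 − r) × 2σ²/n
- ANCOVA: (1 − r²) × 2σ²/n

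The ratio of ANCOVA to final values is therefore 1 − r². The ratio of ANCOVA to change is (1 − r²)/[2(1 − r)] = (1 + r)/2.

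| r | ANCOVA / final values | ANCOVA / change |
|---|---|---|
| 0.3 | 1 − 0.09 = 0.91 | 1.3/2 = 0.65 |
| 0.5 | 1 − 0.25 = 0.75 | 1.5/2 = 0.75 |
| 0.7 | 1 − 0.49 = 0.51 | 1.7/2 = 0.85 |

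To put this on the outcome scale: with 88 per arm, the difference detectable with 80% power by a t test on final values is (1.96 + 0.84) × √(2/88) = 0.42 SD. Multiplying by √(1 − r²) gives 0.40, 0.37 and 0.30 SD for ANCOVA. This is illustration only, since no continuous outcome has a power target.

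**Within-arm tests.** Suppose both arms truly improve by the same amount, d SDs of change, so that there is no treatment difference. By normal approximation the chance that one arm's paired test shows significant improvement is p = 1 − Φ(1.96 − d√88). The arms are independent, so the chance of significance under manual but not under sham is p(1 − p).

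| d (assumed) | d√88 | p | p(1 − p) |
|---|---|---|---|
| 0.2 | 1.88 | 0.467 | 0.249 |
| 0.3 | 2.81 | 0.80 | 0.16 |
| 0.5 | 4.69 | 0.997 | 0.003 |

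The noncentral t distribution gives nearly the same values: 0.248, 0.163 and 0.004. For comparison, a two-sided 5% between-arm test favours manual acupuncture by chance 2.5% of the time.

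The column for p matters as well. At d = 0.5 the manual arm is significant in 99.7% of trials although manual is no better than sham. Discordance is then rare, but the paired result is equally uninformative about treatment.

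**The case against.** The strongest reply is that nothing here is invalid. Under 1:1 randomisation the unadjusted t test is unbiased and holds its type I error, and chance baseline imbalance is already reflected in its standard error. That stands: the first part of the point concerns efficiency, and its size depends on a correlation that the article does not give. At r = 0.3 the gain over final values is only 9%.

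Several stronger readings are tempting, and the article does not support them:

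- **That the primary analysis is affected.** It is not. PASI-50 is binary and is tested by chi-squared or Fisher.
- **That baseline enters only through the paired tests.** PASI-50 is itself defined relative to baseline, and the two-sample t test may be meant for change scores. The comparison with change is shown for that reason.
- **That ANCOVA amounts to a larger trial at no cost.** The 88 per arm was set for proportions, so restating the gain as extra patients would borrow a number that was never planned for these outcomes.
- **That efficacy will be claimed from the paired tests.** No section says so. Section 2.1 states a comparison of manual with sham acupuncture, and section 2.5.1 lists the between-arm test first. The risk is one of misreading.
- **That one-arm-only significance occurs in a quarter of trials.** The product p(1 − p) cannot exceed 0.25, and d = 0.2 lies almost at that maximum. The probability falls quickly for larger improvements.
- **That eligibility builds in regression to the mean.** Section 2.2.1 caps BSA at 15% and sets no minimum severity.
- **That the PASI score lacks an analysis.** It is not listed as a separate outcome, so adding it, or a supportive logistic model for PASI-50, is optional and no part of this point.

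It is also fair to note that anxiety may be analysed as severity grades and that skewed scales go to a nonparametric test. As stated, those analyses are unadjusted too.

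A further defence would be that an article leaves such detail to an analysis plan. That does not help here, because section 2.5.1 positively names the tests.

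**Conclusion.** The point holds for the continuous secondary outcomes: BSA, SF-36, the depression score and the DASS-21 anxiety score when analysed as a score. The stated between-arm test is valid but less precise than it could be. ANCOVA would have 0.51 to 0.91 of the variance of a t test on final values, or 0.65 to 0.85 of that of a t test on change, for assumed r between 0.3 and 0.7. The within-arm paired tests answer no question about treatment. Under equal true improvement and 88 per arm they would point to manual acupuncture alone with probability from about 25% down to 0.3%, for assumed improvements of 0.2 to 0.5 SD of change. This is a worthwhile improvement to a stated method. It does not correct a biased test, and it leaves the primary comparison as it is.

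**What to change.** In section 2.5.1, replace the two-sample t test for continuous secondary outcomes with ANCOVA of the week-13 value on treatment group, with that outcome's baseline value as covariate. Report the adjusted between-arm difference with its 95% confidence interval. For skewed outcomes, name a rank-based or suitably transformed version of the same model and fix the rule for choosing it before unblinding. Any transformation must be defined at zero, since a cleared patient has a BSA of 0. Say whether anxiety is analysed as a score or as grades.

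Remove the within-arm paired tests, and show within-arm change descriptively without p-values.

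The cost is analysis wording only. Both measurements are already scheduled, and sample size, visits and treatment do not change.

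### The PASI-50 primary analysis is left as an unadjusted chi-squared or Fisher test; fixing one baseline-adjusted risk difference in advance, with the sizing test as support, is a cheap, minor improvement

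*Protocol article*

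**What the plan says.** Primary outcomes (2.4.1) defines a binary endpoint, "the proportion of patients with a reduction in the Psoriasis Area and Severity Index (PASI) scores ≥50% compared with baseline". Clinical data analysis (2.5.1) does not name a test for that endpoint. It is covered by one sentence for all categorical data: "Chi-Squared test or Fisher exact test will be used for comparing categorical variables". That section states no rule for choosing between the two tests and names no covariate. It plans an intention-to-treat analysis by a blinded statistician.

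Sample size (2.5.2) does commit to a test, "using the two-sided Z test with pooled variance", with a 5% significance level and 80% power. The assumed rates come from a published study in which "the total curative rate in the acupuncture group was 97.5%, and 87% in the control group". The result is that "88 participants with psoriasis would be required in each group for 80% power", raised to 220 in total for 20% loss. PASI is scheduled before enrolment for all participants (Table 1), so a baseline value is available for adjustment.

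**The concern.** The sizing section names one test. The analysis section allows that test or a second one with different operating characteristics. With response rates near the ceiling there are few non-responders, and Fisher's test is then clearly conservative. The two tests can fall on opposite sides of 5% for the same table, and the text does not say which result would count. A blinded statistician cannot favour a known arm, but still sees both P values.

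The stated method is also unadjusted and yields only a test, although a baseline measure of the same scale is already collected. What is at stake is some power and a clear primary result. The validity of the comparison is not in question.

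**Working it through.** **Inputs.** From Sample size (2.5.2): p1 = 0.975, p2 = 0.87, difference 0.105, mean rate 0.9225, two-sided 5% level, 88 per arm before loss. From Trial design (2.1): 110 per arm randomised.

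**1. The plan's own figure.** The pooled formula is

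n = [1.960·√(2 × 0.9225 × 0.0775) + 0.8416·√(0.975 × 0.025 + 0.87 × 0.13)]² / 0.105²
= (0.7411 + 0.3121)² / 0.011025 = 100.6, so 101 per arm.

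The stated 88 is not reproduced; an arcsine formula gives 89. At 88 per arm the pooled formula gives power Φ[(0.105·√88 − 0.7411)/0.3708] = Φ(0.658) = 74.5%. The loss step does reproduce: 176/0.8 = 220. The 88 is a separate matter, but it means there is no spare power at that size.

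**2. Chi-squared and the pooled Z test are the same test.** Take 84 and 76 responders out of 88. The pooled rate is 160/176 = 0.9091 and the difference is 8/88 = 0.0909. The standard error is √(0.9091 × 0.0909 × 2/88) = 0.0433, so Z = 2.098 and Z² = 4.40. The uncorrected chi-squared statistic for this table is also 4.40.

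**3. Exact power.** This sums the probabilities of two independent binomials over every table that is significant at 5%.

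| Test | 88 per arm | 110 per arm |
|---|---|---|
| Uncorrected chi-squared | 77.7% | 87.5% |
| Fisher throughout | 69.3% | 81.1% |
| Fisher only if an expected count is below 5 (assumed rule) | 76.3% | 87.3% |

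From the unrounded values at 88, the loss is 77.73 − 69.25 = 8.5 points for Fisher throughout and 77.73 − 76.30 = 1.4 under the assumed rule. At 110 it is 87.53 − 81.14 = 6.4 and 87.53 − 87.31 = 0.2. An expected count falls below 5 in 11.3% of trials at 88 and 2.0% at 110.

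With continuity correction the chi-squared test has 66.3% and 79.3%, so the word *uncorrected* should be written out.

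**4. Type I error** at a common rate of 92.25%, 88 per arm: 4.8% for the uncorrected chi-squared and 2.7% for Fisher.

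**5. Tables on which the verdict turns (88 per arm).**

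| Responders | Chi-squared P | Fisher P | Expected non-responders per arm |
|---|---|---|---|
| 84 v 76 | 0.036 | 0.064 | 8.0 |
| 85 v 78 | 0.044 | 0.080 | 6.5 |
| 86 v 79 | 0.029 | 0.057 | 5.5 |

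Under the assumed rule all three would be tested by chi-squared, but the text as written allows either.

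**6. Adjustment for baseline PASI.** The prognostic strength is not in the documents. In simulation at 88 per arm, power rose by about 1.5 to 2 points at an assumed log odds ratio of 0.5 per SD, with type I error near 5%, and by 4 to 6.5 points at 1.0. Some of this need not come from the covariate. A standardised risk difference uses an unpooled variance, and the unpooled sizing formula itself asks for 98 per arm rather than 101.

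**7. A limit of the adjusted model.** If every patient in the acupuncture arm responds, the logistic treatment coefficient has no finite estimate. At the planned rate the chance of this is 0.975^88 = 10.8%, or 0.975^110 = 6.2%.

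**The case against.** The strongest reply has four parts.

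- **No contradiction.** A reader might infer that the analysis departs from the sizing. It does not: the first test named in 2.5.1, if uncorrected, is the sizing test, and nothing says Fisher will be used for PASI-50. This stands in full.
- **The 8.5 points are a worst case.** A reader might take them as the expected loss. They arise only if Fisher is used whatever the counts, with 88 evaluable per arm. The assumed expected-count rule costs 1.4 points, or 0.2 at 110. Even Fisher throughout has 81.1% at 110. This also stands, except that the document states no such rule, and 110 per arm needs an outcome for everyone although 20% loss is planned for.
- **Rule, interval and covariate belong in an analysis plan.** That plan is not shown, so their absence is not an error. An unadjusted chi-squared test is valid for a randomised binary endpoint. This stands. What remains is that 2.5.1 does state a method for categorical outcomes, the primary one included, and that method can be improved.
- **Baseline PASI may add little.** The endpoint is already relative to baseline, and the diagnostic criteria cap the affected area at 15% of body surface, which may narrow the baseline range. This is a fair doubt, and it is why the gain is given only as a range on assumed values.

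**Conclusion.** The point holds as a minor improvement. The documents do not support calling it a contradiction, a fixed loss of 8.5 points, or an error of omission.

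The stated method leaves two tests open for the primary outcome, and they disagree in 8.5% of trials at 88 per arm and 6.4% at 110 under the planned rates. The realistic cost lies between 0.2 points (110 per arm, Fisher only for small expected counts) and 8.5 points (88 per arm, Fisher throughout). Adjustment might add roughly 1.5 to 6.5 points.

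The test comparison rests on the protocol's own rates of 97.5% and 87%. The adjustment gain rests on assumed log odds ratios of 0.5 to 1.0 per SD and could be smaller.

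**What to change.** In 2.5.1, separate PASI-50 from the general sentence and state:

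1. The primary analysis is the risk difference between arms with its 95% CI, from a logistic model with treatment and baseline PASI, standardised over all participants analysed.
2. The unadjusted supporting test is the uncorrected chi-squared test used for sizing.
3. Fisher's test is not used for the primary outcome; the general sentence may stay for other categorical variables.
4. If an arm has no non-responders or the model does not converge, the unadjusted risk difference and the uncorrected chi-squared test are reported as primary. Writing this down beforehand prevents a choice being made after the data are seen.

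The cost is a few sentences and slightly more analysis work, with no new data and no change in sample size. The real downside is reliance on a large-sample interval when non-responders are few, which the planned rates make likely. If the team prefers not to adjust, naming the uncorrected chi-squared test with an unadjusted risk difference and interval still removes the open choice.
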